#### *Other study parameters*

Effect modifiers and possible confounders are:

##### Patient characteristics

• Dental anxiety will be measured with the MDAS [39], which consists of five items and the Monitoring Blunting Dental Scale [44].

• Anticipated pain will be measured after the patients’ preoperative assessment. This will be measured with an 11-point VRS [36].

• Anticipated anxiety will be measured after the patients’ preoperative assessment. This will be measured with an 11-point VRS [45].

• Whether the patient is funded by the NHS or privately.

• Whether the patient is a referral patient or a regular (in-house) patient.

• Self-reported oral health status will be measured with one question after the patients’ preoperative assessment [46].

• Demographic characteristics will be completed as part of the questionnaire that patients complete after treatment. Data on age, sex and education will be collected.

• Previous cancellations will be measured with one question (self-reported).

##### Treatment characteristics

• The type of treatment

• The length of treatment

• The treating dentist

• Sedation

### Data analysis

The data will be recorded and analyzed using SPSS 20.0. All data will be analyzed using an intention-to-treat analysis. Descriptive statistics will be calculated. Discrete variables will be summarized by frequencies or proportions. Continuous variables will be reported as means and standard errors or medians and range (depending on the distribution of the variables). Data will be checked for baseline differences between the treatment arms. If baseline differences do occur for any of the variables, they will be added to subsequent models to compensate for those differences using an analysis of covariance approach.

Analyses of covariance (ANCOVAs) will be performed for each of the outcome measures with VR condition (that is, natural, urban or control) as the independent variable and baseline dental anxiety as the covariate, including planned contrasts to explore specific hypotheses. Contrasts for VR condition will be based on comparisons of VR (both natural and urban environments combined) with the no VR control group (comparison 1), natural VR with urban VR (comparison 2), natural VR with the control group and urban VR with the control group (Table 2 gives an overview of specific predictions being tested).

**Table 2 T2:** Overview of the specific comparisons for each prediction

	**Prediction**	**Comparison 1:**	**Comparison 2:**	**Comparison 3:**
		**virtual reality (both natural and urban environments) vs no virtual reality (control group)**	**natural virtual reality vs urban virtual reality**	**(a) natural virtual reality vs control**

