### Randomization process

Patients will be allocated to one of the three conditions by computer randomization using the ralloc command in the STATA software package. Randomization will be stratified by sedation (RA; yes or no) and the dentist who performs the treatment (dentist 1 or dentist 2). Randomization will be concealed via sequentially numbered opaque sealed envelopes and will be revealed by the dentist or nurse who will start the VR, immediately prior to commencing the treatment.

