#### *For both patient groups*

Patients will be randomized when they attend their scheduled treatment appointment (that is, after baseline data has been recorded). If a patient decides that he or she no longer wants to participate in the study, the baseline data will be discarded. When undergoing their scheduled dental treatment, patients will be exposed to either one of the VR conditions (natural or urban VR environment) or the control condition (usual care). Standard clinical procedures will be followed and when treatment will be started, patients will either be handed a pair of VR goggles (when assigned to the VR groups) or a pair of protective glasses (when assigned to the standard care group). Patients in the VR groups will receive an explanation of how to use the controller by a member of staff. Heart rate will be monitored during dental treatment by a staff member using a pulse oximeter on a finger of the hand that is not operating the controller. The output of the pulse oximeter throughout the treatment session will be recorded by the dentist or nurse. After treatment, staff will record the treatment characteristics and patient characteristics. The patient will be asked to complete a questionnaire in the waiting room before leaving the dental practice. This questionnaire takes about 10 minutes to complete and consists of four parts; treatment experience, VR experience, dental experience and demographic information. The patient will be provided with an envelope, in which to seal the questionnaire.

One week after treatment, patients will receive a phone call, during which we will ask them about their memories and dental anxiety. This phone call will be made by one of the members of the research team and will take between 5 and 10 minutes. After responding to the questions, patients will be debriefed and will be asked if they would like to receive the results of the study. If patients ask questions regarding their clinical care during this interview, it will be tactfully explained to them that the interviewer is not a clinician and they will be directed to the practice for a response to any such queries.

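### Beyond baseline dental anxiety, covariates are chosen by observed baseline imbalance, so the final model depends on the data and tends to omit the stratification factors

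*Protocol article*

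**What the plan says.** The Data analysis section of the protocol article first sets the trigger, "Data will be checked for baseline differences between the treatment arms", and then the consequence, "If baseline differences do occur for any of the variables, they will be added to subsequent models to compensate for those differences". It names no test, no threshold and no closed set of variables.

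The same section prespecifies one covariate. The ANCOVA for each outcome has VR condition "as the independent variable and baseline dental anxiety as the covariate, including planned contrasts to explore specific hypotheses".

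The only list of candidates is under Other study parameters, introduced by "Effect modifiers and possible confounders are". Its Treatment characteristics part includes "The length of treatment" as well as sedation and the treating dentist.

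On timing, the Procedure section says "Patients will be randomized when they attend their scheduled treatment appointment (that is, after baseline data has been recorded", and later "After treatment, staff will record the treatment characteristics and patient characteristics". Table 1 agrees.

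The Randomization process section says "Randomization will be stratified by sedation (RA; yes or no) and the dentist who performs the treatment (dentist 1 or dentist 2". Neither factor is named as a term in the analysis model.

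**The concern.** Allocation is random and concealed, so a baseline difference between arms carries no information beyond chance. A covariate earns its place by predicting the outcome, whether or not it happens to be balanced. An imbalance trigger skips strong predictors that are balanced and admits weak ones that are not. Three things follow.

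- The final model for the three primary outcomes (remembered pain, intrusive thoughts, vividness) is settled only after the arms have been compared. With no threshold stated, what counts as a difference is left to judgement.
- The factors thought important enough to stratify on are the ones least likely to be admitted, because stratification holds them near balance.
- Length of treatment is among the listed confounders but is observed only after randomization. The Background says that anxious patients take longer to treat, and the Additional predictions say that VR will reduce stress. Length is therefore plausibly something VR could change, and adjusting for it could then distort the treatment effect.

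**Working it through.** **1. The plan's own figure.** Inputs from Sample size: SD 1.3, difference 0.82, 30 per group, two VR groups against control (60 v 30), two-sided 0.05, power 0.80.

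Detectable difference = 1.3 × √(1/30 + 1/60) × (1.960 + 0.842) = 0.814. Power at 0.82 is 0.805 (normal) or 0.797 (noncentral t). Per-group inflation: 30/0.85 → 36, total 108; 36/0.92 → 40, total 120. The stated 90, 108 and 120 reproduce. They do not depend on the covariate rule.

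**2. How often chance changes the model.** Other study parameters lists 15 variables: MDAS, Monitoring Blunting scale, anticipated pain, anticipated anxiety, funding, referral status, oral health, age, sex, education, previous cancellations, treatment type, treatment length, dentist and sedation. Remove MDAS (taken as the baseline anxiety measure already in the model) and the two stratifiers: 12 remain. Remove length as well, since it is not a baseline measure: 11 remain.

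Assume each is screened at 5%, independently:

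- 11 variables: 1 − 0.95^11 = 0.43
- 12 variables: 1 − 0.95^12 = 0.46

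**3. What the selection does to the test.** Simulation with 30 per arm and 5,000 runs per setting. Candidates are independent, screened by a three-arm F test at 0.05; the contrast is VR against control. The number of candidates, the screen and the correlations are assumptions. Each cell shows no candidates / imbalance rule / all candidates fixed in advance.

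| Candidates; correlation of each with outcome | Type I error | Power at 0.82 |
|---|---|---|
| 12; 0 | 0.045 / 0.046 / 0.050 | 0.79 / 0.78 / 0.73 |
| 12; 0.20 | 0.052 / 0.040 / 0.049 | 0.79 / 0.80 / 0.95 |
| 12; 0.25 | 0.048 / 0.035 / 0.048 | 0.80 / 0.81 / >0.99 |
| 2; 0.40 | 0.052 / 0.046 / 0.049 | 0.81 / 0.82 / 0.93 |
| 2; 0.50 | 0.047 / 0.041 / 0.049 | 0.80 / 0.81 / 0.97 |

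The Monte Carlo standard error of a type I error near 0.05 is √(0.05 × 0.95/5000) = 0.003. The rule never exceeds the nominal level. It is clearly conservative only where the candidates predict the outcome well, and there it recovers almost none of the available precision. Where they predict nothing, fixing all 12 loses power, so the prespecified list should be short.

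**4. Length of treatment.** Simulation with 4,000 runs, true effect −0.82, and length adjusted for only when it differs between VR and control at 0.05. The shift in length and its standardized coefficient on the outcome (0.3 or 0.5) are assumptions.

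| VR effect on length | Flagged as different | Mean estimate (coefficient 0.3; 0.5) |
|---|---|---|
| −0.5 SD | about 60% | −0.67; −0.57 |
| none | about 5% | −0.82; −0.82 |
| +0.5 SD | about 60% | −0.96; −1.08 |

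Bias appears only if VR changes length, and its direction follows the direction of that change.

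**The case against.** The strongest reply is that the base model is fixed. Baseline dental anxiety enters every ANCOVA whatever the balance, and only further terms are conditional. That stands: a reader might infer from the rule that no covariate is settled in advance, and the Data analysis section contradicts this.

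Second, the rule speaks of baseline differences, length of treatment is not a baseline measure, and the Data analysis section does not refer to the confounder list. A reader might infer that the trial will adjust for length; the protocol never says so. What remains is an ambiguity. Time of recording does not settle what counts as baseline here, because age, sex, education and previous cancellations are also collected after treatment (Table 1).

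Third, a reader might suspect that selecting covariates from the data produces false positives. The simulation does not bear this out.

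Fourth, the frequency in step 2 rests on assumptions. Counting all 15 listed variables would give 1 − 0.95^15 = 54%, but that includes the covariate already fixed, two factors balanced by design and one variable that is not baseline. Anticipated pain, anticipated anxiety and the blunting scale are plausibly correlated, so independence is doubtful too. The figure is the chance that the rule fires and does not measure harm.

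Last, an analysis plan that is not shown may close the list. It may, but the article already commits to the imbalance trigger, so this is a stated rule and not an omitted detail.

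**Conclusion.** The point holds in a limited form. All covariates beyond baseline dental anxiety are selected by observed imbalance, which makes the final primary models data-dependent and tends to exclude sedation and dentist. Under an independent 5% screen of 11 or 12 variables, chance alone would alter the model in about 43% to 46% of trials.

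The harm is lost precision and tests that are at most slightly conservative. In the settings with prognostic candidates, power was 0.80 to 0.82 under the rule against 0.93 or more with the same covariates fixed. That gain depends wholly on prognostic strength, which the protocol does not report for any candidate, so it should not be read as the gain to expect from sedation and dentist. With candidates of no prognostic value the ordering reverses (0.78 against 0.73).

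Bias from length of treatment is conditional on two things the protocol does not establish: that the rule would be applied to length, and that VR changes it. The protocol should be corrected, but the rule does not invalidate the planned comparisons.

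**What to change.** In the Data analysis section:

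1. Delete the sentence that adds variables when baseline differences are found.
2. State that every effect model includes baseline MDAS, sedation (RA yes or no) and dentist as covariates, whatever the observed balance.
3. Report baseline characteristics by arm descriptively, with no role in choosing the model.
4. State that variables which treatment may affect after randomization, such as length of treatment, are not covariates in effect models. Define the exclusion by what allocation could influence and not by when the form is filled in, since demographics are recorded after treatment.

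Any further baseline covariate, such as anticipated pain for the pain outcomes, is optional and should be named in advance if wanted.

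The cost is wording and two degrees of freedom. With 90 followed up, three arms and baseline anxiety leave 90 − 3 − 1 = 86 residual degrees of freedom; adding sedation and dentist leaves 84. Trial status reports only two patients randomized at submission, so at that stage the change could be made without knowledge of results.

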**Methods/design:**

The effectiveness of VR distraction will be examined in patients 18 years or older who are scheduled to undergo dental treatment for fillings and/or extractions, with a maximum length of 30 minutes. Patients will be randomly allocated into one of three groups. The first group will be exposed to a VR of a natural environment. The second group will be exposed to a VR of an urban environment. A third group consists of patients who receive standard care (control group). Primary outcomes relate to patients’ memories of the dental treatment one week after treatment: (a) remembered pain, (b) intrusive thoughts and (c) vividness of memories. Other measures of interest are the dental experience, the treatment experience and the VR experience.

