#### *Referral patients*

Referral patients will receive a letter from the practice about their appointment date in the post. The patient information leaflet about the study will be included. On average, this is about 12 weeks before the treatment takes place.

When the patient comes in for a preoperative assessment, informed consent will be obtained, at the end of this appointment. On average, this is 4 weeks before the treatment appointment. After obtaining informed consent, and at the end of the preoperative assessment appointment, the dentist or nurse will hand a baseline questionnaire to the patient. The patient will be asked to complete these questions at the practice before going home. Patients will be asked to complete a dental anxiety questionnaire, reporting their oral health status and anticipated pain. Completing the questionnaire will take between 5 and 10 minutes.

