### Outcome measures

#### *Main study parameters*

We developed a questionnaire that assessed intrusive thoughts of the experience and vividness of memories of the experience. This questionnaire is based on the Alcohol Craving Experience Questionnaire [35]. This was developed to assess craving based on the elaborated intrusion theory and measures vividness of memories and intrusive thoughts. The questions to measure memories and intrusive thoughts were used in our pilot work and showed sufficient reliability in that study (Cronbach’s alpha of respectively 0.69 and 0.81). They are slightly adapted to fit the purposes of the current study.

• Vividness of memories will be measured with five items on an 11-point verbal rating scale (VRS).

• Intrusive thoughts about the experience will be measured with three items on an 11-point VRS.

• Remembered pain will be measured with an 11-point VRS [36].

• Patients will respond to an open-ended question about the three things they remember most and to indicate, for each of these three things, how pleasant or unpleasant their thoughts were. They will also be asked how well they remember what the dentist said.

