##### Treatment experience

• Pain will be measured with an 11-point VRS [36].

• Discomfort will be measured with two questions on an 11-point VRS [25].

• Stress will be measured with a self-reported measure and a physiological indicator (heart rate). The self-reported measure consists of five items from the tension dimension from the Profile of Mood States [37]. Heart rate will be monitored using a pulse oximeter and the output will be recorded.

• Time perception will be measured with one question in which patients are asked to estimate how many minutes they think they have been wearing the VR goggles or protective glasses [38].

• Perceived control will be measured with an 11-point VRS.

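### Anticipated pain, recorded before randomization, enters the pain models only if the arms happen to differ on it, so precision on remembered pain may be given up

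*Protocol article*

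**What the plan says.** The abstract lists the primary outcomes as "a) remembered pain, (b) intrusive thoughts and (c) vividness of memories". The scales of the three pain ratings are given in different places:

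- Main study parameters: "Remembered pain will be measured with an 11-point VRS [36".
- Treatment experience (additional prediction 1): "Pain will be measured with an 11-point VRS [36".
- Patient characteristics, under the heading for modifiers and confounders: "Anticipated pain will be measured after the patients’ preoperative assessment. This will be measured with an 11-point VRS [36".

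The baseline questionnaire is described in the same terms for referral and in-house patients: "Patients will be asked to complete a dental anxiety questionnaire, reporting their oral health status and anticipated pain". It precedes allocation: "Patients will be randomized when they attend their scheduled treatment appointment (that is, after baseline data has been recorded".

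The Data analysis section then prescribes an ANCOVA for each outcome "with VR condition (that is, natural, urban or control) as the independent variable and baseline dental anxiety as the covariate". The paragraph before it adds a conditional route: variables on which the arms differ at baseline are added to later models. Baseline dental anxiety is therefore the only unconditional covariate, and anticipated pain is a conditional one.

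**The concern.** A baseline covariate improves precision to the extent that it predicts the outcome, whether or not the arms differ on it. In a randomized trial a baseline difference is a chance event. The plan makes the use of anticipated pain depend on that event. If the arms are balanced on it, which is the usual case, it stays out, and whatever variance it explains in the pain ratings remains in the error term.

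For dental anxiety after treatment and at one week, the common covariate is the outcome's own baseline value. For the pain outcomes it is not, and a more closely related pre-randomization rating is already in the database. Remembered pain is a primary outcome, and the Background singles it out as the feature of memory expected to improve. The Sample size section says that recruitment is limited by the patients available in the practice, so lost precision cannot easily be bought back with more patients.

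**Working it through.** **Inputs** (Sample size section): SD 1.3 and detectable difference about 0.82, both for intrusive thoughts; two-sided 0.05; power 0.80; 90 followed up, both VR groups (60) against control (30).

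**Step 1. Reproduce the plan's figure.** The standard error is 1.3 × √(1/30 + 1/60) = 0.2907. By normal approximation the detectable difference is (1.960 + 0.842) × 0.2907 = 0.814. By noncentral t with 86 degrees of freedom (90 patients, 3 arms, 1 covariate) it is 0.824. The stated 0.82 is thus the combined-VR contrast with no allowance for a covariate gain. Recruitment also reproduces: 30/0.85 gives 36 per arm (108), and 36/0.92 gives 40 per arm (120).

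**Step 2. Effect of adding anticipated pain.** Let r be the partial correlation of anticipated with remembered pain, given arm and baseline dental anxiety. The residual SD is multiplied by √(1 − r²), and one degree of freedom is spent (86 to 85). The documents give neither r nor an SD for remembered pain, so r is an assumed range and SD 1.3 and 0.82 are borrowed for scale only. Power is by noncentral t for a difference of 0.82.

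| r | Variance removed | Detectable difference | Power, 60 vs 30 | Gain (points) |
|---|---|---|---|---|
| 0 | 0% | 0.82 | 79.7% | – |
| 0.2 | 4% | 0.81 | 81.2% | 1.5 |
| 0.3 | 9% | 0.79 | 83.2% | 3.5 |
| 0.4 | 16% | 0.76 | 86.1% | 6.4 |
| 0.5 | 25% | 0.71 | 89.6% | 9.9 |

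In patients followed up, 90/(1 − r²) − 90 gives about 4, 9, 17 and 30 extra for r = 0.2, 0.3, 0.4 and 0.5. The lost degree of freedom is repaid once r exceeds about √(1/86) = 0.11.

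**Step 3. Contrasts of 30 versus 30.** Table 2 of the article requires these for hypothesis 3 and additional prediction 1. With 56 and 55 degrees of freedom, power at 0.82 is 67.0% without anticipated pain, 74.5% at r = 0.4 and 79.1% at r = 0.5. Using the error term of the three-arm model raises each by about half a point.

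**Step 4. Allow for what dental anxiety already explains.** In Step 2 a partial correlation is applied to an SD that has not been adjusted for anxiety. Suppose dental anxiety correlates 0.35 with the outcome (an assumption). The starting SD is then 1.3 × √(1 − 0.35²) = 1.218 and the starting power 84.6%. Adding anticipated pain gives:

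- r = 0.2: 86.0%, gain 1.4 points
- r = 0.3: 87.7%, gain 3.1 points
- r = 0.4: 90.1%, gain 5.5 points
- r = 0.5: 93.0%, gain 8.4 points

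**Step 5. How large r might be.** Take assumed marginal correlations of 0.4 (anticipated with remembered pain), 0.35 (anxiety with remembered pain) and 0.5 (anticipated pain with anxiety). Then r = (0.4 − 0.35 × 0.5)/√((1 − 0.35²)(1 − 0.5²)) = 0.28. With 0.3 in place of 0.4, r = 0.15. Overlap with anxiety can therefore put r in the lower part of the range.

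**The case against.** The strongest case against is that nothing here is wrong: a prespecified ANCOVA with a pre-randomization covariate gives a valid comparison, and the sample size claims no covariate gain. That stands. A reader might infer that leaving out anticipated pain biases the VR contrasts or undermines the stated power; the documents support neither.

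A reader might also take anticipated pain for the baseline value of remembered pain, because scale and citation agree. That goes too far. It is an expectation given on average 4 weeks (referral) or 25 days (in-house) before treatment, whereas remembered pain is recall one week after it. A shared response format does not make a shared construct. It is a related predictor, and the parallel with dental anxiety is only partial.

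The size is also open to challenge. The Background links dental anxiety to pain, so the planned covariate may already carry part of the information; Steps 4 and 5 show the effect. The SD and the difference belong to another outcome, so no power figure above describes remembered pain itself. These points lower the size and certainty of the gain but leave its direction unchanged unless r is below about 0.1, where the effect either way is trivial.

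Finally, one common covariate that is also the hypothesized moderator is a coherent choice, and the article lists other candidate predictors, such as anticipated anxiety, without ranking them. This is a fair argument for restraint. It does not justify letting chance imbalance decide whether a likely predictor is used. Nor is this merely detail left to an analysis plan, because the article states both the covariate and the rule for adding others.

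**Conclusion.** The point holds as a modest efficiency gain of unknown size. The unconditional model for the pain outcomes omits a plausible predictor that is already collected before randomization, and admits it only on a criterion unrelated to its prognostic value.

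For an assumed partial correlation of 0.2 to 0.5, residual variance falls by about 4% to 25%. On the borrowed intrusive-thoughts inputs this is worth about 1.5 to 10 points of power for VR against control, or about 1.4 to 8.4 points if dental anxiety correlates 0.35 with the outcome. The upper end should not be read as expected, since no document supports a correlation of 0.5.

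The abstract names remembered pain first among the primary outcomes, but the hypotheses and the Methods list place it third and the sample size rests on intrusive thoughts. Its position in the abstract therefore adds no weight; its status as a primary outcome is what matters.

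**What to change.** Add one sentence to the Data analysis section: in the ANCOVAs for remembered pain at one week and for treatment pain (additional prediction 1), anticipated pain is a covariate beside baseline dental anxiety, whatever the observed baseline balance. Leave the models for the other outcomes unchanged.

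The cost is one degree of freedom out of about 86. No new data are needed, because the item is in the baseline questionnaire of both patient groups. If some patients lack the item, a simple baseline imputation that ignores arm and outcome keeps them in the intention-to-treat analysis. The Trial status section reports two patients randomized at submission, so at that point the change could still have been prespecified.

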### Aims and hypotheses

The main aim of the project is to determine whether the use of virtual nature during dental treatment can improve recollections of treatment and the overall dental experience. Additionally, we will look at the moderating role of patients’ baseline level of dental anxiety in these effects. A third aim is to test whether the content of the VR distraction can make a difference for its effectiveness by comparing two types of virtual environment, a natural environment and an urban environment.

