#### *Objectives*

1. Determine the effectiveness of VR in improving recollections of treatment and the overall dental experience.

2. Determine the role of patients’ level of dental anxiety and test whether the use of VR could be especially beneficial for patients suffering from dental anxiety.

3. Determine any effect relating to the content of the VR.

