#### *Overall hypotheses:*

1. Virtual reality exposure will lead to less intrusive thoughts, less vivid memories, less remembered pain and better overall dental experiences.

2. Dental anxiety will moderate the proposed effects under hypothesis 1. Patients with more dental anxiety will benefit more from the use of VR than patients with less dental anxiety.

3. The natural VR environment will be more effective than the urban VR environment.

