### Sample size

Given the novel approach of this study, there is little comparable research available to use for a sample size calculation. We are also somewhat restricted by the number of potential patients available within a given time period in the dental practice. However, we do have data from our own pilot work in a simulated dental setting, which we have used to make an informed estimate of the required sample size for the current study.

The sample size calculation (with a power of 0.80, significance level of 0.05 and based on 2-sided testing) is based on one of the main outcomes related to memories, ‘intrusive thoughts’, as measured with an 11-point verbal rating scale. In our pilot study, the standard deviation for this outcome in our control group was 1.25 and we have conservatively used an estimated standard deviation of 1.3 in this sample size calculation. Based on these assumptions, and comparing the two VR groups against the control group, following up a total sample size of 90 patients (that is, 30 per group) would allow the detection of a between-group difference of around 0.82 units (that is, a moderate effect size). Since drop-outs are unavoidable when collecting follow-up data, this number needs to be adjusted for the estimated drop-out rate. In our simulation study, we had a drop-out rate of 10% for collecting the follow-up data, but since we paid participants for participation in that study (although they received their pay after the simulated treatment and before participating in the follow-up interview), we anticipate a higher drop-out rate for this study, and have allowed for a 15% drop-out rate. Adjusting the sample size for this drop-out rate results in a sample of 108 patients needing to be recruited.

The use of technical computer equipment is associated with the risk of technical failures. In the pilot study we had to exclude 6 of 75 participants because the VR crashed or the remote stopped working during the simulated treatment and the participant was no longer able to interact with the VR environment. Several improvements in the VR program have been made since, such as putting force fields in place that restrict the area of virtual exploration, but we still anticipate the exclusion of participants because of technical issues. We will therefore increase the sample size by a further 8%, resulting in a total recruitment target of 120 for this study (that is, 40 patients per group).

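### Hypothesis 2 (baseline dental anxiety moderates the VR effect) is mapped to the same VR-versus-control contrast as hypothesis 1, and no condition-by-anxiety term is stated, so the analysis as written does not test objective 2

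*Protocol article*

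**What the plan says.** Moderation is a declared question of the trial. Under Aims and hypotheses the authors write that "we will look at the moderating role of patients’ baseline level of dental anxiety in these effects". Objective 2 is to "test whether the use of VR could be especially beneficial for patients suffering from dental anxiety". Overall hypothesis 2 reads "Dental anxiety will moderate the proposed effects under hypothesis 1", and adds: "Patients with more dental anxiety will benefit more from the use of VR than patients with less dental anxiety".

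The Data analysis section gives one model for every outcome, an ANCOVA "with VR condition (that is, natural, urban or control) as the independent variable and baseline dental anxiety as the covariate". The planned contrasts are all contrasts of condition: "Contrasts for VR condition will be based on comparisons of VR (both natural and urban environments combined) with the no VR control group (comparison 1"), then natural against urban VR, then each VR group against control. Table 2 links each prediction to these comparisons. Hypothesis 1 and hypothesis 2 each have one tick, both under comparison 1.

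Dental anxiety also appears in the list headed "Effect modifiers and possible confounders are" (Other study parameters), with no analysis attached to that label. Two instruments are named there under dental anxiety: the MDAS and the Monitoring Blunting Dental Scale.

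**The concern.** Hypothesis 2 says that the size of the VR effect depends on baseline anxiety. That is an interaction. A contrast between groups in a model where anxiety enters only as a covariate estimates a single VR effect. It is the same test for hypothesis 2 as for hypothesis 1, and it can come out either way whether or not moderation exists.

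Two errors follow if the plan is carried out literally. A significant comparison 1 could be reported as support for hypothesis 2 although VR helps all patients equally. Conversely, real moderation with a small average effect would go unnoticed. Whether anxious patients gain more is one of the three stated objectives.

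**Working it through.** **1. The model and the hypothesis side by side.** Let V be the pooled VR-versus-control contrast and A the centred baseline anxiety.

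- Model with anxiety as covariate only: E(Y) = a + d·V + b·A. The VR effect is d at every value of A.
- Model that expresses hypothesis 2: E(Y) = a + d·V + b·A + g·V·A. The VR effect is d + g·A.

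Hypothesis 1 concerns d and hypothesis 2 concerns g. Comparison 1 tests d. (Natural versus urban is left out of the notation for brevity.)

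**2. The plan's own figures reproduce.** Inputs from Sample size: SD 1.3; 30 per group, so 60 VR against 30 control; "with a power of 0.80, significance level of 0.05 and based on 2-sided testing".

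- SE = 1.3 × √(1/60 + 1/30) = 0.291.
- Detectable difference = (1.960 + 0.842) × 0.291 = 0.81 (normal), or 0.82 with the t distribution on 88 df. The article states about 0.82.
- Drop-out: 30/0.85 = 35.3, so 36 per arm, 108 in all. Technical failures: 36/0.92 = 39.1, so 40 per arm, 120 in all.

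The arithmetic is sound, and it is for the main effect only.

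**3. What the stated contrast says about moderation.** Simulation of 10,000 trials per row: 30 per arm, residual SD 1.3, anxiety standard normal, prognostic slope 0.3, two-sided 5%. The interaction model carries the product of anxiety with both comparison 1 and comparison 2, leaving 90 − 6 = 84 df.

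| Average VR effect (units) | Moderation (units per SD of anxiety) | Comparison 1 significant | Comparison 1 × anxiety significant |
|---|---|---|---|
| 0.82 | 0 | 79% | 4.8% |
| 0 | 0.82 | 5.7% | 76% |
| 0.82 | 0.82 | 75% | 76% |
| 0 | 0 | 4.9% | 5.0% |

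Comparison 1 responds to the average effect and essentially not to moderation.

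**4. Power of the right test.** If anxiety had exactly unit variance and the same spread in each arm, the SE of g would equal the 0.291 of step 2. The detectable slope difference would then be 0.81 (normal) to 0.82 (t, 84 df) per SD. Anxiety varies from sample to sample, and with normally distributed anxiety simulation gives somewhat less power:

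- 0.82 per SD: about 76%
- 0.85 per SD: about 79%
- 0.87 per SD: about 80–81%, so 80% needs about 0.86
- 0.41 per SD: about 27% (29% by the closed form)

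A 50/50 high/low split would double the SE. The detectable difference between the halves would be 1.63 to 1.65 units, with 29% power for a difference of 0.82. This favours keeping anxiety continuous.

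**Assumptions not in the documents:** the moderation sizes, the prognostic slope, the distribution of anxiety, and the use of 1.3 as the residual SD within arms.

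**The case against.** The best reply is that Table 2 lists which groups are compared, not which model terms are fitted, and has no column in which an interaction could be shown. Hypothesis 2 is worded as moderation of the effects under hypothesis 1, and hypothesis 1 is comparison 1. The tick could therefore mean that the effect being moderated is comparison 1. The article never says that the covariate is purely additive, it lists anxiety among effect modifiers, and it condenses a fuller protocol that may state the term.

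That reading is possible, so a reader should not infer that the authors have no intention of testing moderation or that the trial cannot answer objective 2: the baseline data are collected. What does not stand is the claim that this is only omitted detail. The article gives a model, lists its contrasts as contrasts of condition, and assigns hypothesis 2 to one of them. Nowhere does it state an interaction, slope or subgroup test.

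Two stronger inferences also fail. A reader might conclude that unequal slopes invalidate comparison 1 altogether. They do not: under randomisation comparison 1 still estimates an average VR effect, so hypothesis 1 is unaffected. A reader might also take the plan's 0.82 as the moderation detectable with 80% power. That rests on the fixed-variance closed form; with normally distributed anxiety, power there is about 76%.

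**Conclusion.** The point holds for hypothesis 2. As written, objective 2 is assigned to a contrast that tests the average VR effect, and no stated term tests moderation. This is structural and does not depend on the simulated figures, which only show its size: about 79% significant results for comparison 1 when there is an effect of 0.82 but no moderation, and about 6% when there is moderation of 0.82 per SD but no average effect. It should be corrected before analysis, because one of three objectives has no valid test in the text and the assigned test can mislead.

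The primary outcomes, the sample size calculation and the test of hypothesis 1 are not in question. Even with the right term, 90 patients give 80% power only for a slope difference of about 0.86 units per SD of anxiety and under 30% for 0.41, given residual SD 1.3 and roughly normal anxiety. A null interaction would therefore not show that moderation is absent.

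**What to change.** - For hypothesis 2, add to the ANCOVA the product of comparison 1 (VR versus control) and baseline dental anxiety, continuous and centred. Make its coefficient, with 95% CI, the test of hypothesis 2.
- Name the moderator, for example baseline MDAS, since two instruments are listed under dental anxiety.
- Change the Table 2 entry for hypothesis 2 to comparison 1 × baseline anxiety.
- Keep the model without the interaction for hypothesis 1.
- State that the sample size powers the main effect only, give the approximate power for the interaction with its assumptions, and say that a null result does not exclude moderation.

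The cost is one model term, one table entry and two or three sentences. No new data are needed, because baseline anxiety is already collected from both referral and in-house patients. At submission two patients had been randomized (Trial status), so at that point the change could have been fixed before outcome data accrued.
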